### Interview and questionnaires

Eligible individuals will be invited at the outpatient clinic, after their regular appointment, to participate in the study. At study entry, patients will undergo a baseline interview (Fig. 1). Interviews will be performed by a trained professional using a standard pre-coded questionnaire. The following information will be collected by interview or review of medical records: (i) clinical and epidemiological data: previous diagnoses, including chronic heart failure, peripheral arterial disease, acute myocardial infarction (AMI), chronic arterial disease, chronic obstructive pulmonary disease (COPD), dyslipidemia and diabetes; Canadian Cardiovascular Society (CCS) Functional Classification of Angina grade at the moment of the interview [10]. (ii) Biological factors: age and sex. (iii) Socioeconomic factors: skin color, social class, literacy, income, and schooling. (iv) Lifestyle: alcohol consumption, smoking, and practice of physical activities. (v) Use of medications: dose and type of medications, adherence to drug treatment (measured by an adapted version of the Brief Medication Questionnaire). (vi) Laboratory tests and medical procedures performed.

**Fig. 1 Fig1:**
[figure not shown]
Flow Diagram of Study Design

### Intervention

The intervention will be discharge from the tertiary outpatient clinic and referral to the primary care facility nearest to the home address, with clinical support from an existing telemedicine platform and a toll-free hotline (TelessaúdeRS/UFRGS). Prompt access to the tertiary outpatient clinic will be ensured in acute situations following agreement between primary physicians and teleconsultants. The toll free line is accessible to primary care physicians is available Monday through Friday, from 8:00 a.m. to 5:30 p.m. [11].

A TelessaúdeRS/UFRGS team designated for the project includes one specialized cardiologist with access to the patient’s electronic record, whose role will be to aid primary care physicians in patient management, and a medical student dedicated to manage and monitor the study flowchart.

The control group will undergo the routine follow-up scheme, with appointments scheduled every six months or once yearly at the outpatient Ischemic Cardiopathy Clinic at HCPA.

### Randomization

Patients eligible for inclusion will be randomized 1:1 using random block sizes of six and four, by a computerized list provided by randomization.com. The investigator in charge of randomization will not be involved in determination of eligibility or assessment of outcomes. Group assignment will be performed by opening a sealed opaque envelope in front of the patient after signature of the informed consent form and completion of the initial research questionnaire. After that, the groups will be managed as follows (Fig. 1):Telehealth group (intervention group): the patient will be discharged from the tertiary care outpatient clinic and directed to a primary care facility (Basic Health/Family Health Strategy unit) previously identified according to residential address. At the primary care facility, patients will book a routine appointment within two months. For that, the patient will bring the discharge note, comprising all relevant information about the case, medical prescriptions, and a counter-reference note with therapeutic planning. The TelessaúdeRS/UFRGS team will contact the basic health unit and provide access to the telehealth platform for follow-up monitoring. A teleadvisory will be scheduled between the medical teleconsultants and the primary physicians within two months after outpatient clinic discharge to discuss clinical management of the patient. Furthermore, primary physicians can call the support team at TelessaúdeRS/UFRGS whenever they have doubts about the clinical management. Patients will be interviewed by telephone at four and eight months of follow-up using the standardized instrument used at study entry. The calls will be made by independent evaluators, hired and trained specifically for this purpose. An appointment will be booked at 12 months of follow-up for final evaluation of the patient.Control group: patients will undergo the usual flow routine during the study period. Patients will be interviewed by telephone using the standardized instrument at four and eight months of follow-up. An appointment will be booked at 12 months of follow-up for final evaluation of the patient. Ifclinical status is stable, the patient will no longer attend the tertiary outpatient clinic for follow-up.

For all patients (intervention and control groups), the 12-month appointment will focus on evaluation of symptoms, episodes of disease decompensation, and adherence to treatment. Patients who do not show up for the 12-month appointment will be contacted by telephone. If the patient is not found, the study team will contact the primary care facility to determine the patient’s clinical status.

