### Study population and sample size

The study population will be selected among patients from the Ischemic Heart Disease outpatient clinic at HCPA, a tertiary care university hospital in South Brazil. All clinic patients have CAD defined by the presence of at least one of the following: documented history of myocardial infarction, surgical or percutaneous myocardial revascularization, lesion > 50 % in at least one coronary artery assessed by angiography, or presence of angina and positive noninvasive testing of ischemia [8].

Study participants will undergo standard anamnesis and medical examination to verify clinical stability and discharge criteria.

The sample size was calculated as 140 patients in each group—considering a non-inferiority margin of 10 % and incidence of 92 % of the main outcome, that is, maintenance of Canadian Cardiovascular Society Functional Classification (CCS) 12 months after the start of follow-up. This was based on the rate of patients with increase in angina to a higher CCS reported by a previous study for the control group receiving optimal treatment for CAD [9]. An additional 10 % margin was added to account for losses to follow-up. For calculation of sample size, a ß of 0.9 and an α of 0.05 (two-sided) were considered.

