### Inclusion and exclusion criteria

Individuals of both genders, aged ≥ 18 years, with a diagnosis of CAD and CCS I or II at the moment of enrollment, without cardiovascular events requiring hospital admission during the previous year, will be selected for the study. Verification of discharge criteria will be performed by the medical team running the clinic, without interference from the investigators.

Patients who have been followed-up at the clinic for less than 1 year, unstable patients needing medication adjustments, patients performing diagnostic evaluation at the moment of enrollment, or those who do not agree with the outcome of randomization will be excluded.

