### Outcome measures and assessment procedures

Telephone interviews aim to identify changes in functional class or clinical events taking place over the follow-up period.

The final 12-month interview will evaluate the same components assessed in the initial interview, in order to determine improvement/worsening of clinical status. All patients will undergo blood tests with serum lipids and glucose evaluation.

The primary outcome is maintenance of CCS I or II at 12 months.

Secondary outcomes focus on risk factors. Control of risk factors will analyze variations of at least 5 % in the following pre and post-intervention measurements [12]:systemic blood pressure;controlled dyslipidemia: LDL < 100 mg/dL;glycated hemoglobin (in the presence of diabetes);abstinence from tobacco smoking;about 150 min/week of regular physical activity.

Additional secondary outcomes include health care access variables, such as: medical appointment in primary care facility taking place within not more than six months after referral, with review of medications and issue of prescriptions; and disease instability during the 12-month follow-up, defined as the need for seeking emergence care due to cardiovascular disease: acute chest pain; heart failure decompensation; acute arrhythmias; stroke.

Given the objective nature of the outcomes, the safety of the intervention, and the brief follow-up period, endpoint adjudication and data monitoring committees will not be appointed. No interim analyses are proposed. At the 4 and 8-month telephone interviews patients will be asked about possible unintended effects of the trial, and will receive guidance as required. After the trial, patients will be readmitted to the outpatient clinic if continued care at a primary care facility is not available.

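### Baseline CCS class is known before allocation and predicts the primary outcome, but adjustment for it is left to a P < 0.10 screen; fixing it in advance gives a small, nearly free gain in precision

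*Protocol article*

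**What the plan says.** All references are to the protocol article.

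- **Entry** (Inclusion and exclusion criteria): patients come in "with a diagnosis of CAD and CCS I or II at the moment of enrollment". The expected split between the two classes is not given.
- **Baseline measurement** (Interview and questionnaires): the interview records the "Functional Classification of Angina grade at the moment of the interview".
- **Allocation** (Randomization): "Patients eligible for inclusion will be randomized 1:1 using random block sizes of six and four". No stratification factor is named. The envelope is opened "after signature of the informed consent form and completion of the initial research questionnaire", so class is known by then.
- **Primary outcome** (Outcome measures and assessment procedures): "The primary outcome is maintenance of CCS I or II at 12 months".
- **Sample size** (Study population and sample size): 140 per group, "considering a non-inferiority margin of 10 % and incidence of 92 % of the main outcome". On the source of the 92%: "This was based on the rate of patients with increase in angina to a higher CCS reported by a previous study". On error rates: "a ß of 0.9 and an α of 0.05 (two-sided) were considered". A further 10% is added for losses.
- **Analysis** (Statistical analysis): logistic regression is planned for the primary and secondary outcomes. Covariates reaching P < 0.10 one at a time go into the multivariate model. Baseline CCS class is not mentioned.

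**The concern.** If failure means reaching class III or IV, the endpoint itself makes baseline class prognostic: class II is one grade from failure, class I two. The variable is binary, already collected, and available before allocation. A trial with such a variable would normally fix its use in advance, in the analysis at least.

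Here its use depends on the data. At 8% failure and 126 evaluable patients per arm, about 252 × 0.08 ≈ 20 failures are expected, and a univariate screen on 20 events may or may not select class. The adjustment set for the one comparison that decides non-inferiority is therefore unknown until the outcomes are seen. Precision is at stake, together with having a primary analysis that is settled beforehand.

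**Working it through.** **1. Reproduce the stated sample size.** Inputs from the sample size section: success 0.92 in both arms, margin 0.10, power 0.90. The variance per patient is 0.92 × 0.08 = 0.0736.

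n per arm = (z₁₋α + z₀.₉₀)² × 2 × 0.0736 / 0.10²

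- One-sided 0.05: (1.645 + 1.282)² × 0.1472 / 0.01 = 126.06, rounded up to 127. Then 127 × 1.1 = 139.7, that is 140, as stated.
- One-sided 0.025 (the literal two-sided 0.05): 155, then 171 with the same 10% addition. This does not match.

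The figure of 140 therefore reproduces only with a one-sided 0.05. Both levels are carried below. With 10% loss, 140 × 0.9 = 126 per arm are evaluable.

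**2. Unadjusted precision and power.** SE = √(2 × 0.0736 / 126) = 0.0342, or 3.42 points. Power = Φ(0.10/0.0342 − z) = Φ(2.926 − z), which is 0.833 at one-sided 0.025 and 0.900 at one-sided 0.05.

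**3. What class could explain.** Assumptions, not in the documents: class II share s = 0.25–0.50, failure risk ratio of II to I r = 2–8, overall failure 0.08.

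- Class I risk f₁ = 0.08 / [(1 − s) + s·r]; class II risk f₂ = r·f₁.
- Between-class variance B = s(1 − s)(f₂ − f₁)²; fraction of variance removed = B / 0.0736.
- Adjusted SE = √(2 × (0.0736 − B) / 126).

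| s | r | f₁ | f₂ | Variance removed | Adjusted SE (points) | Power, 0.025 | Power, 0.05 |
|---|---|---|---|---|---|---|---|
| 0.25 | 2 | 0.064 | 0.128 | 1.0% | 3.40 | 0.837 | 0.903 |
| 0.25 | 3 | 0.053 | 0.160 | 2.9% | 3.37 | 0.844 | 0.907 |
| 0.25 | 5 | 0.040 | 0.200 | 6.5% | 3.31 | 0.857 | 0.916 |
| 0.25 | 8 | 0.029 | 0.233 | 10.6% | 3.23 | 0.872 | 0.926 |
| 0.50 | 2 | 0.053 | 0.107 | 1.0% | 3.40 | 0.836 | 0.902 |
| 0.50 | 3 | 0.040 | 0.120 | 2.2% | 3.38 | 0.841 | 0.905 |
| 0.50 | 5 | 0.027 | 0.133 | 3.9% | 3.35 | 0.847 | 0.910 |
| 0.50 | 8 | 0.018 | 0.142 | 5.3% | 3.33 | 0.852 | 0.913 |

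**4. Chance imbalance.** The SD of the between-arm difference in class II share is √(2s(1 − s)/126), or 5.5 points at s = 0.25 and 6.3 at s = 0.50. Multiplied by (f₂ − f₁), the SD of the resulting shift in the risk difference is 0.34–1.11 points (95% range from about ±0.7 to ±2.2). This is a component of the 3.42-point SE, not an addition to it.

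**5. Simulation** (126 per arm, class II share 20–50%, risk ratio 3 or 5, Wald limits, 40,000 runs per scenario).

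| Randomisation | Analysis | Type I error, nominal 0.025 | Type I error, nominal 0.05 |
|---|---|---|---|
| Unstratified | Unadjusted | 0.026–0.029 | 0.054–0.056 |
| Unstratified | Stratified | 0.029–0.031 | 0.056–0.058 |
| Stratified | Unadjusted | 0.019–0.025 | 0.041–0.050 |

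Under unstratified randomisation, power at one-sided 0.025 was 0.828–0.833 unadjusted and 0.842–0.863 stratified, in line with step 3. The third row shows that stratifying the lists without adjusting the analysis makes the test conservative and does not recover the full gain.

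**The case against.** **The screen may bring class in.** The screening sentence follows the one on Cox regression but is not limited to it. Simulating it with 252 evaluable patients, 25–50% class II and Fisher's test at P < 0.10, class would be selected in about 72–78% of trials at a risk ratio of 3, 93–97% at 5, and 99% or more at 8. Where the gain is largest, the rule would nearly always pick class up. This stands, so it would be wrong to say that the primary comparison ignores baseline class. What remains is that the choice depends on the data. Moreover, logistic regression gives an odds ratio, while the margin is an absolute difference.

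**Chance imbalance.** A reader might infer that an imbalance in class threatens the validity of the non-inferiority conclusion. The documents do not support that. Randomisation leaves no bias, the shift can go either way, and the unadjusted standard error already contains it.

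**No promised power is lost.** The planned 90% was calculated without adjustment and holds at 126 per arm with one-sided 0.05. The drop to 83% comes from the label two-sided in the sample size section. That is a separate and larger matter. This also stands.

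**The one-grade versus two-grade premise depends on the endpoint.** The sample size section takes its rate from any rise in CCS, and the Abstract speaks of maintaining the baseline class 1 or 2. If any rise is failure, both classes are one grade away and the structural argument falls. The outcome section is the explicit definition, so the point follows it, but the texts need reconciling.

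**Unstratified blocks are legitimate.** In a single-centre trial of 280 patients this is a reasonable choice. Stratified lists are therefore offered only as an option.

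**Conclusion.** The point holds as a modest improvement in precision and prespecification, not as an error that undermines the design. Over the assumed range (25–50% class II, risk ratio 2–8, 8% failure, 126 evaluable per arm), adjusting for baseline class removes about 1–11% of the variance. Power goes from 0.83 to about 0.84–0.87 at one-sided 0.025, or from 0.90 to about 0.90–0.93 at one-sided 0.05. In patients, 126 × 1–11% is roughly 1 to 13 per arm. The upper end needs a risk ratio of 8 with only 25% class II; at a ratio of 2 or 3 the gain is about one power point or less.

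The result rests on the class mix and class-specific risks, which the documents do not give, and on failure meaning class III or IV at 12 months.

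**What to change.** 1. **Statistical analysis section.** State that the primary comparison is the difference in proportions stratified by baseline CCS class (I or II), as a Mantel-Haenszel risk difference with its confidence interval, and that the limit is compared with the 10-point margin. State that this stratum is fixed in advance and not subject to the P < 0.10 rule. With about 20 events, Wald limits ran slightly above nominal in the simulations with and without adjustment, so name the interval method too.
2. **Randomization section, optional and only if enrolment has not started.** Prepare separate block lists and envelope sets for CCS I and CCS II with the same block sizes. Do this only together with the stratified analysis. If enrolment has begun, keep the existing list and make change 1 alone.
3. **Endpoint.** Reconcile the sample size and outcome sections on whether any rise in CCS, or only reaching class III or IV, is failure.

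The cost is a few lines of wording and, if the option is taken, a second set of envelopes. No extra patients or measurements are needed.

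### Patients not found at month 12 are traced in both arms only through primary care, which provides trial follow-up for the intervention arm alone, so ascertainment may differ by arm

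*Protocol article*

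**What the plan says.** The protocol article sets the 12-month tracing chain at the end of the Randomization section, for both arms together: "For all patients (intervention and control groups), the 12-month appointment will focus on evaluation of symptoms". Two fallbacks follow. The first is the telephone: "Patients who do not show up for the 12-month appointment will be contacted by telephone". The second is the facility: "If the patient is not found, the study team will contact the primary care facility to determine the" clinical status of that patient. The chain ends there; no other source is named and nothing is split by arm.

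The Intervention section says where each arm is followed. For the intervention arm: "The intervention will be discharge from the tertiary outpatient clinic and referral to the primary care facility nearest to the home address". For controls: "The control group will undergo the routine follow-up scheme". Their visits are described as "appointments scheduled every six months or once yearly at the outpatient Ischemic Cardiopathy Clinic at HCPA". Under Randomization, the intervention patient's facility is "previously identified according to residential address". It receives a discharge note and a treatment plan through the patient, is contacted by the telehealth team, gets access to the platform and has a scheduled teleconsultation. Nothing similar is described for a control patient's local facility.

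The primary outcome (Outcome measures and assessment procedures) is keeping Canadian Cardiovascular Society (CCS) class I or II at 12 months, analysed by intention to treat (Statistical analysis).

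**The concern.** The rule looks symmetric because one sentence covers both arms, but the source it names stands in a different relation to each. For an unfound intervention patient, the team asks the site the trial made responsible for coronary follow-up, which knows the allocation and is part of the strategy under test. For an unfound control, it asks a site to which the trial gave no role, while the tertiary clinic that saw the patient is not named.

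Two things could follow. Status may be recovered more often in one arm, and it may come from a different kind of informant. Few failures are expected: at the planned 92% rate, 140 x 0.08 = 11.2 per arm. The loss allowance, 10% of 140 = 14 per arm, is of the same order, so how unfound patients are classified can matter to a non-inferiority comparison.

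This is a stated data-collection rule and not a detail left to an analysis plan. Later analysis can choose how to treat missing values, but it cannot make differently sourced values comparable.

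**Working it through.** **Inputs from the documents** (Study population and sample size): 140 per group, expected rate 92%, margin 10 points, 10% allowance for losses.

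**The plan's own figure.** n = 2 x 0.92 x 0.08 x (z_alpha + z_power)^2 / 0.10^2. With one-sided alpha 0.05 and power 0.90 this gives 127, and 127 x 1.1 = 139.7, so 140 is reproduced. With the printed two-sided 0.05 it gives 155 before losses, which does not reproduce 140. That is a separate matter; nothing below depends on it.

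**Assumptions, not in the documents.** The true rate is 92% in both arms, so any difference is distortion.
- f = share unfound after visit and telephone. I take 10%, an upper-end value because the telephone will reach some patients.
- q = true rate of keeping class I or II among the unfound, from 0.50 to 0.92, equal in both arms.
- r = share of the unfound whose status is recovered correctly.

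**Formulas.**
- Rate among those found: p = (0.92 - f q)/(1 - f).
- Complete-case rate in an arm: [(1 - f) p + f r q] / [(1 - f) + f r].
- Rate if unrecovered patients count as failures: (1 - f) p + f r q, so the arm difference is f q (r_I - r_C).

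**Worked example**, f = 0.10 and q = 0.50: p = (0.92 - 0.05)/0.90 = 0.9667.
- Recovery 80% versus 50%: intervention (0.87 + 0.04)/0.98 = 0.9286; control (0.87 + 0.025)/0.95 = 0.9421; difference -1.4 points.
- Recovery 100% versus 0%: 0.9200 - 0.9667 = -4.7 points.

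Intervention minus control, in points, f = 10%:

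| q | p | Complete case, 80% v 50% | Complete case, 100% v 0% | Unrecovered = failure, 100% v 0% |
|---|---|---|---|---|
| 0.92 | 0.9200 | 0.0 | 0.0 | +9.2 |
| 0.80 | 0.9333 | -0.4 | -1.3 | +8.0 |
| 0.70 | 0.9444 | -0.7 | -2.4 | +7.0 |
| 0.50 | 0.9667 | -1.4 | -4.7 | +5.0 |

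**Variations.**
- f = 5%, 100% versus 0%: complete case 0.0 to -2.2; unrecovered as failure +2.5 to +4.6.
- f = 10%, 80% versus 50%, unrecovered as failure: 0.10 x 0.50 x 0.30 = +1.5 to 0.10 x 0.92 x 0.30 = +2.8.
- f = 10%, 100% versus 0%, complete case, every recovered patient reported stable whatever the truth: +0.3 to +0.8.
- Equal recovery (50% in both arms), complete case: 0.0 for every q.
- The lowest q compatible with 92% overall at f = 10% is 0.20, where p = 1. The 100% versus 0% complete-case shift would then be -8.0, but this requires every patient found to have kept class.

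**The case against.** The strongest reply is that the procedure is written identically for both arms and is only the third step, after the appointment and the telephone call. Both arms also have telephone interviews at four and eight months, which help keep contact. Few patients may ever reach this step. That stands, and it limits the size of the problem.

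Several stronger readings are tempting but go beyond the text:

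- **That primary care treats only the intervention arm.** No section says so. The article describes a universal health system with primary care near the home, and controls may well use a local unit. The text supports only that trial follow-up is placed there for the intervention arm alone.
- **That recovery does differ and the comparison is biased.** No recovery rate is given for either arm. Under complete-case analysis, bias also needs recovered and unrecovered patients to differ in outcome, or the reports to be wrong. That unfound patients are those most likely to have worsened is plausible but not stated.
- **That the facility's report is entered as the CCS grade.** The article says only that clinical status is sought, not how it is used.
- **That the distortion could consume the whole margin.** With 126 found patients at 92%, (126 x 0.92 + 14)/140 = 92.8% against 126 x 0.92/140 = 82.8% does give +10.0 points. It needs the full 10% unfound, 100% versus 0% recovery, every recovered patient called stable, and missing counted as failure. The last rule appears nowhere in the article, and missing-data handling may sit in a plan not shown. The result is simply 14/140, the missing fraction.

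It can also be said that record review is not excluded for controls, since Interview and questionnaires lists medical records as a data source and the final interview covers the same components. But the tracing sentence does not make the hospital record a fallback, so the asymmetry in the written rule remains.

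**Conclusion.** The point holds as a possible bias, not an established one. As written, the last-resort source is the trial follow-up site for one arm and not for the other, so recovery and source of the 12-month status may differ by arm among patients missed at both the visit and the telephone call.

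Size and direction do not follow from the documents. Under the assumptions above, moderately unequal recovery gives a small complete-case shift against the intervention. The extreme case reaches about half the 10-point margin with q no lower than 0.50. Counting unrecovered patients as failures reverses the sign and favours the intervention, the direction that matters more for a non-inferiority claim. A reader should not conclude that the primary result would be invalid. This is a cheap improvement to a stated rule.

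**What to change.** Change the tracing sentence so that, for every patient in either arm not found by visit or telephone, the study team checks the same two sources: the HCPA hospital record and the primary care facility. In addition:

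- record the source of each 12-month outcome (visit, patient telephone call, hospital record, facility, none) and tabulate it by arm;
- apply one rule, common to both arms, to any status not obtained from the patient;
- add a sensitivity analysis limited to CCS grades obtained from the patient by visit or telephone.

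Same sources do not guarantee equal recovery, and the table by arm will show whether it was achieved.

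The cost is one changed sentence, one field on the form and a little extra record checking. The article mentions electronic-record access only for the project cardiologist, so access for tracing may have to be arranged. Some outcomes will be excluded from the sensitivity analysis.
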